## Abstract

**Background:**

In response to the US opioid epidemic, significant national campaigns have been launched to expand access to `opioid use disorder (MOUD). While adoption has increased in general medical care settings, specialty addiction programs have lagged in both reach and adoption. Elevating the quality of implementation strategy, research requires more precise methods in tailoring strategies rather than a one-size-fits-all-approach, documenting participant engagement and fidelity to the delivery of the strategy, and conducting an economic analysis to inform decision making and policy. Research has yet to incorporate all three of these recommendations to address the challenges of implementing and sustaining MOUD in specialty addiction programs.

**Methods:**

This project seeks to recruit 72 specialty addiction programs in partnership with the Washington State Health Care Authority and employs a measurement-based stepped implementation-to-target approach within an adaptive trial design. Programs will be exposed to a sequence of implementation strategies of increasing intensity and cost: (1) enhanced monitoring and feedback (EMF), (2) 2-day workshop, and then, if outcome targets are not achieved, randomization to either internal facilitation or external facilitation. The study has three aims: (1) evaluate the sequential impact of implementation strategies on target outcomes, (2) examine contextual moderators and mediators of outcomes in response to the strategies, and (3) document and model costs per implementation strategy. Target outcomes are organized by the RE-AIM framework and the Addiction Care Cascade.

**Discussion:**

This implementation project includes elements of a sequential multiple assignment randomized trial (SMART) design and a criterion-based design. An innovative and efficient approach, participating programs only receive the implementation strategies they need to achieve target outcomes. Findings have the potential to inform implementation research and provide key decision-makers with evidence on how to address the opioid epidemic at a systems level.

**Trial registration:**

This trial was registered at ClinicalTrials.gov (NCT05343793) on April 25, 2022.

**Supplementary Information:**

The online version contains supplementary material available at 10.1186/s13012-022-01239-y.

Contributions to the literature 
• Stagewise Implementation-To-Target–Medications for Addiction Treatment have elements of a sequential multiple assignment randomized trial (SMART) design and a criterion-based design that employs a measurement-based stepped implementation-to-target approach within an adaptive trial design to improve access to medications for opioid use disorder (MOUD).• The trial is conducted in a real-world healthcare setting (specialty addiction programs). • MOUD access in specialty addiction programs has lagged in both reach and adoption—making it challenging for patients with opioid use disorder who need and want medications to receive it. • Findings could advance drug abuse treatment research by optimizing strategies to implement MOUD.

## Background

The 21st Century Cures Act allocated unprecedented funding to combat the US opioid epidemic. Its mission is to reduce opioid over-prescribing, improve access to overdose rescue medications, and increase the adoption and delivery of medications for opioid use disorder (MOUD) [1, 2]. Efforts have been primarily focused on expanding access to MOUD. The Substance Abuse and Mental Health Services Administration (SAMHSA) State Targeted Response and the State Opioid Response grants to 57 US states and territories sought to expand access to methadone, buprenorphine, and naltrexone across a variety of settings and systems [2–4].

While indications of improved access across a variety of settings exist, an ironic gap persists [5–10]. Primary care practices, emergency departments, and the criminal justice system have increasingly adopted MOUD, but traditional specialty addiction treatment programs have not progressed. Currently, only 35.5% of addiction treatment programs offer MOUD [6]. As such, only 15% of patients in specialty addiction treatment with opioid use disorder (OUD) are receiving MOUD [5, 11]. In fact, general medical practice settings are now twice as likely to offer MOUD than specialty addiction treatment programs [12–14].

Specialty addiction treatment programs are under pressure to implement MOUD but face many barriers [7, 10, 15–18]. Public health systems now support MOUD in policy and financing, but multiple contextual barriers persist, ranging from an abstinence-based philosophy that conflicts with pharmacological approaches, a lack of network connectivity with other health care organizations, and program structure and workflows based entirely on psychosocial interventions and peer recovery supports [19–21]. Although there has been progress among some specialty programs, most lag behind in their efforts to offer MOUD to their clients [11].

### Implementation research to improve MOUD access

This study builds on our prior implementation research. In specialty addiction programs, a cluster randomized controlled trial with addiction treatment organizations located in the State of Washington utilized a multi-level strategy—NIATx (Network for the Improvement of Addiction Treatment) [22–26] delivered through external facilitation (NIATx-EF) to implement integrated mental health services for persons with co-occurring psychiatric and substance use disorders [27]. Overall, the NIATx-EF implementation strategy had a significant effect on improving integrated services [28] and increasing patient access to substance use and psychotropic medication, as well as decreasing wait times from diagnosis to medication receipt [29, 30]. We also found that NIATx-EF was effective, more effective with NIATx-EF adherence, and surprisingly, that 10% of organizations achieved target implementation outcomes early on with only enhanced feedback using a standardized quality measure, Dual Diagnosis Capability in Addiction Treatment (DDCAT).

Four system-level, naturalistic cohort evaluation studies focused on implementing MOUD in public health care systems. In Vermont, a learning collaborative implementation strategy showed increased guideline adherence and reduced variation but no change in reach or adoption [31]. Two California-based studies examined how exposure to different implementation strategies impacted reach (number of patients receiving MOUD) and adoption (number of eligible providers prescribing MOUD). While both studies showed a significant change in reach and adoption, the influence of specific implementation strategies was mixed [32–34]. The final study found that access to implementation support: external facilitation, learning sessions, didactic webinars, and enhanced monitoring and feedback (EMF), resulted in significant improvement in implementation quality [35]. Although mitigated by the lack of controlled experimental designs, two major takeaways were that some practices make changes with a “soft touch” implementation strategy support—such as EMF—using standardized measures like the DDCAT and target performance measures, and offering a buffet of implementation support options is unnecessarily burdensome, inefficient, and costly.

### Multi-level implementation strategies to improve MOUD access

Implementation science continues to enhance scientific rigor by systematically examining implementation strategies as the “interventions” of implementation. More recently, experts have called for implementation strategies to be examined by (1) their discrete and combined components, (2) conceptualized mechanisms of action, (3) how they may be tailored or adapted to context or other factors, (4) how they may be delivered with fidelity, (5) how enrolled participants engage and finish, (6) how alternative strategies compare with one another on implementation outcomes, and (7) how much they cost [36–39]. Although exemplar studies featuring some of these expert recommendations for implementation strategies do exist, none to date features all, and none is in the critical field of implementing MOUD.

The new paradigm for implementation research (Fig. 1) in addiction health services must extend beyond just opening the “black box” of implementation context and outcomes [33]. Specifically, the quality of implementation strategy research must examine the contents of the “black box” as shown in the final level as depicted in Fig. 1 to better understand how and why an implementation endeavor succeeds or fails. In response to expert recommendations, more precise methods are necessary to tailor implementation strategies rather than a one-size-fits-all-approach, document participant engagement and fidelity to the delivery of the strategy, and conduct economic evaluations to inform decision making and policy. Research has yet to incorporate all three of these recommendations to address the challenges of implementing and sustaining MOUD in specialty addiction programs. The Stagewise Implementation-To-Target–Medications for Addiction Treatment (SITT-MAT) study will address both the public health care and the scientific quality gaps.

**Fig. 1 Fig1:**
[figure not shown]
Opening the “black box” of implementation

## Methods

### Aims and objectives

The overarching goals of the SITT-MAT project are to equally advance implementation science and to solve a persistent public health care problem, access to addiction medications in specialty addiction treatment programs. The study aims to (1) evaluate the relative impact of a sequence of four implementation strategies on target outcome criteria within a stepped measurement approach which includes a randomized implementation trial, (2) examine contextual moderators and mediators of performance on target outcomes as a function of implementation strategy step, and (3) document the costs associated with participating in and delivering the sequence of implementation strategies and to model costs per implementation strategy to achieve target outcome criteria.

### SITT-MAT conceptual model

Advances in the characterization of context, and the evaluation of outcomes, demonstrate methodological progress for implementation science. Our dynamic non-linear conceptual model is based upon matching implementation strategies to levels of contextual determinants (i.e., barriers or facilitators) to produce desired outcomes (Fig. 2) [38, 40, 41].

**Fig. 2 Fig2:**
[figure not shown]
SITT-MAT conceptual model: aligning multi-level strategies with contextual determinants

The characterization and measurement of the contextual determinants can be organized at three levels: outer (systems and community), inner (the organization or setting), and individual (providers and staff) perspectives along with perceptions of the implemented intervention are determinants of successful or unsuccessful implementation [40, 42]. These determinants can be assessed through the Consolidated Framework for Implementation Research (CFIR) which provides an inventory of barriers and facilitators (Table 1) across the three different levels [40].

**Table 1 Tab1:** System, organizational, and individual contextual barriers to MOUD

**System-level factors**	System-level factors include policy, community, and financial levers. In MOUD implementation by specialty addiction programs, system barriers include myths about prohibitive policies, historical isolation from other health care providers, and norms that do not endorse MOUD
**Organization-level barriers**	Organization-level barriers include leaders who may not support MOUD, a culture of anti-MOUD as “just another crutch” and inflexible daily schedules
**Individual contextual barriers**	Individual contextual barriers are manifest in one’s own personal experience with addiction recovery, the lack of physicians or any licensed prescriber, and addiction counselors’ fears about the “professionalization” of the field

Implementation strategies might address potential barriers at each level to implement MOUD, but presently, no solid empirical bases for selection and tailoring based on contextual determinants exist [43, 44]. Instead, we were guided by four criteria in our selection of implementation strategies: (1) the evidence for each strategy, (2) the standard practice of using the strategy to address typical implementation problems at the determinant level, (3) our own research, and (4) the incremental effort and cost associated with each strategy.

### Study design

We will deploy an adaptive implementation strategy design that incorporates a nonrandomized evaluation and a randomized implementation trial (Fig. 3). The stagewise implementation-to-target, stepped approach to implementation, with adaptation based on actual performance, is soundly based on our prior research and a reasonable conceptual model. The stagewise implementation design is like the idea of offering a “light touch” implementation strategy to programs that require minimal support to achieve targets, and progressing towards additional strategies that are more intense, resource-demanding, and costly, but only if needed. Four implementation strategies are staged sequentially, based on the program-level response (Table 2).

**Fig. 3 Fig3:**
[figure not shown]
SITT-MAT adaptative implementation strategy design

**Table 2 Tab2:** SITT-MAT implementation strategies

**Strategy**	**Description**
**Enhanced monitoring and feedback (EMF)**	All participants will receive EMF initially and throughout the course of the active implementation phase of the study. EMF consists of the following: • Performance data gathered and reported by the program for reach and adoption on a quarterly basis • Reach, adoption, and effectiveness data summaries and IMAT results for each program, and, in comparison to the entire sample, will be reflected back to clinical leaders and staff members, via dashboards
**NIATx/MAT academy**	Two-day workshop: • Day 1 – Provide participating programs with rationale, clinical practice, and program integration with MOUD. [name] and regional MOUD expert leader prescribers will present clinical aspects of MOUD, integrating MOUD into culture and workflow, and managing complex situations • Day 2 – Provide participating programs with an overview of NIATx principles and tools. [name], who has used the NIATx academy to train over 1000 individuals, will provide participants with the critical skills (e.g., building change teams, conducting walkthroughs) and tools (e.g., process flow charts, nominal group technique) needed to implement rapid cycle Plan-Do-Study-Act (PDSA) process improvement
**NIATx-internal facilitation (NIATx-IF)**	Internal facilitators will receive training on how to provide coaching within their organization. For 9 months, they will do the following: • Support teams to harness resources toward systemic change and improvement • Employ a range of concepts and tools to provide individualized support to teams • Help teams to practice and hone their skills to optimize performance • Focus on team relationships and communications • Participate in group coaching calls involving IFs from other NIATx-IF programs and moderated by NIATx expert to discuss common change-related issues, progress, and successful tactics
**NIATx-external facilitation (NIATx-EF)**	For 9 months, organizations in the NIATx-EF study arm will work with one of 4 experienced consultant NIATx-external facilitators (EFs). The EF will do the following: • Meets with clinic staff to plan change projects, review ongoing change efforts, discuss successes, and offer guidance on planning future change projects using PDSA cycles • Makes a 1-day site visit during the 1st quarter of the implementation period • Leads monthly 1-h phone calls

#### Implementation strategies

The first implementation strategy is enhanced monitoring and feedback (EMF), which has some elements of “audit and feedback” widely used in the Veterans Health Administration [44–46]. This strategy is provided to all participating programs. The EMF incorporates the use of performance data, compiled, and reflected back to programs with normative status. It targets contextual determinants at the system and organizational level. As we found in our prior studies to improve co-occurring capacity [28, 47], we hypothesize that an EMF condition, providing dashboard feedback on reach and adoption plus a measure of implementation quality, will produce quick outcomes for some programs. We predict that this strategy will most likely work with programs with fewer barriers that do not need as much support to meet target outcomes.

The second implementation strategy is the NIATx/MAT Academy that is provided if EMF is not immediately successful. The academy is a 2-day training/workshop that will bring together members of specialty addiction programs from across the state, debunk myths about MOUD and abstinence-based philosophy, and instruct on MOUD content and NIATx implementation processes. This strategy aligns with systems and organizational determinants. Our prior research found a positive impact of learning sessions on reach and adoption, as well as implementation quality [31, 33, 35].

All programs that do not achieve or sustain target outcome criteria by the end of Phase 3 (12 months from baseline) will be randomized to either of the remaining two implementation strategies—NIATx Internal Facilitation (NIATx-IF) and NIATx External Facilitation (NIATx-EF). The NIATx-IF strategy features an internal change leader (employee) who will help other staff gain skills and efficacy to implement changes and address barriers in attitude and beliefs. Thus, determinants at the individual and organizational levels are the focus of the NIATx-IF implementation strategy (Fig. 2). NIATx-EF is an evidence-based implementation strategy that is widely used and studied [45]. NIATx-EF features an external expert or coach. The coach leverages their expertise and knowledge to guide staff in implementing changes, help employees gain confidence and skills, and address potential obstacles including stigma and attitudes [22, 48]. For the same reasons as NIATx-IF, NIATx-EF is tailored to issues at the organization and individual levels. IF and EF models have been systematically studied and compared [46, 49, 50]. Although there is evidence for both IF and EF, with better outcomes for EF, the cost for EF is likely greater than for IF [49]. Using the procedures employed in a previous implementation trial, we will balance the two groups before randomization [51]. We will then use a randomized cluster group trial design to compare NIATx-IF to NIATx-EF.

In our study design, programs that “graduate” to the sustainment/follow-up arm but then fail to maintain the criteria of success for two consecutive quarters will have two opportunities to rejoin the active implementation strategy phases (Fig. 3). The first opportunity where a program on Path 1 could re-enter is at the end of Phase 3 if they do not sustain improvements after receiving the EMF strategy. The second opportunity for a program on Path 2 to re-enter would be at the end of Phase 4 if they do not sustain improvements after receipt of the EMF and NIATx/MAT Academy implementation strategies. There are thus five possible paths a program might take in this study. Months in the active implementation stage range from 6 (Path 1) to 30 (Path 5). The sustainment period ranges from 12 months (Path 5) to 36 months (Path 1). The path followed by a program depends on when it meets (and sustains) implementation targets.

This study was reviewed by the Stanford University Institutional Review Board and approved as a minimal risk study (eProtocol # 66,398). The project is registered at ClinicalTrials.gov (NCT05343793). The Standards for Reporting Implementation Studies (StaRI) reporting standards and checklist (Additional File 1) was used [52].

### Participants

We will enroll 72 addiction treatment programs from the State of Washington. Programs that are either residential (detoxification or rehabilitation) or outpatient (intensive outpatient or outpatient) levels of care are eligible. The community addiction treatment programs in Washington are comparable to addiction treatment programs nationwide in MOUD implementation. Specifically of all addiction treatment programs in the state, 72% do not offer MOUD. Therefore, despite the potential for limiting inference outside of one system, findings should be generalizable. Opioid treatment programs (i.e., methadone clinics) are not eligible because they are already engaged in MOUD.

Near the conclusion of the project, efforts will be made to examine aggregate administrative data obtained from the State of Washington Health Care Authority, regarding MOUD activity (reach, adoption), the population of addiction treatment programs across the state. This will enable a naturalistic comparator to the volunteer effects of study participation and also the influence of historical factors (e.g., major changes in policy, financing, or public health circumstances [viral epidemics]) that might have impacted the entire state.

A qualitative approach to understanding the participating organizations’ experience with contextual factors, the sequence of strategies, and changes in the culture and practice would be of great methodological value. To achieve this goal, we will conduct key informant interviews with 10% of participating organizations, stratified to represent the range of participant characteristics, e.g., start-up vs. scale up, urban/rural, level of care (residential/inpatient; outpatient/intensive outpatient).

### Outcomes and data collection

Three categories of measures are collected in the SITT-MAT study: (1) primary implementation outcomes (Aim 1), (2) contextual determinants (Aim 2), and (3) implementation strategy participation, fidelity, and cost measures (Aim 3). Although all measures interrelate to address the study aims, each category is principally associated with an aim as specified below.

### Implementation outcomes (Aim 1)

Primary outcomes are organized by the RE-AIM taxonomy and the Addiction Care Cascade [53–55]. Reach, Effectiveness, Adoption, Implementation (quality of MOUD), and Maintenance (sustainment) are augmented by timely access and retention in care—the latter two are elements of the Addiction Care Cascade (Table 3). The Reach, Adoption, and Effectiveness outcomes have been similarly collected using the identical procedure in our recently completed study [35].

**Table 3 Tab3:** Primary outcome definitions

	Aim 1	Aim 1 definition
**Aim 1 primary outcomes**	Reach	The proportion of program patients with OUD and receiving MOUD (buprenorphine, naltrexone) within the index quarter
	Adoption	The number of onsite integrated DEA x-waivered prescribers of buprenorphine or prescribers of naltrexone, who are prescribing MOUD
	Effectiveness	*Access*: The proportion of patients prescribed MOUD who start the medication within 72 h of OUD diagnosis. For patients requiring detoxification for naltrexone, *Access* will be operationalized as the proportion of patients who start the medication within 72 h of when it is safe *Retention*: The proportion of patients who are retained in continuous care for at least 6 months from the start of medication, or if in time-limited care situations (e.g., residential detoxification) for the entire treatment episode
	Implementation	Changes in the IMAT Index at the assessment points are indicated in Fig. 3
	Maintenance	To assess sustainment, the primary outcomes detailed above will be monitored quarterly, even as an organization moves into the sustainment phase. IMAT data collection for the organizations in the sustainment phase will follow the same timeline as that of organizations still engaged in the active implementation (post each strategy, and at 1-year follow-up) Together, these four outcomes (RE-AI) will reflect the sustainment of gains made during the active implementation phase as a function of (a) implementation strategies, (b) contextual determinants, and (c) participation in and fidelity to the implementation strategies

Implementation quality will be measured using the Integrating Medications for Addiction Treatment (IMAT) Index. The IMAT is a newer measure built upon the same framework and methodology as its widely adopted predecessors [26, 56, 57]. The IMAT, comprised of 45 items clustered into seven dimensions (Additional File 2), integrates MOUD guidelines, expert consensus recommendations, the OUD care cascade, and best practice information into a team-assessment benchmark measure of current and future state MOUD capability and practice [58]. Confirmatory factor analyses support the validity of the IMAT Total Score, as well as the validity of each dimension. Reliability scores for each dimension range between 0.70 and 0.95. The IMAT has been useful to systems, organizations, and teams as an objective measure of current state MOUD practice and as a blueprint for measurable practice change. Like the DDCAT, the IMAT is transparent in depicting what is needed to score a 3 or 5 for practices seeking to improve implementation quality.

Three primary outcomes-Reach, Adoption, and Implementation (IMAT) serve as implementation targets to determine the stagewise path of participating organizations. A program will meet the SITT-MAT adaptative assessment criteria if (1) greater than or equal to 50% of their patients with OUD are receiving a MOUD (Reach), (2) the program has an integrated MOUD prescriber who is employed or contracted by the program (Adoption), and (3) the IMAT Total Score is greater than or equal to 3 (Implementation). By including a measure of intervention quality (IMAT), our study will overcome the threat of implementation without fidelity being no better or even harmful [59, 60]. The Reach and Adoption primary outcome measures will be gathered at baseline and quarterly for the duration of the trial, to the end of the sustainment phase and the IMAT-SC will be assessed at baseline and at the end of each phase (Fig. 3).

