### Data analysis

#### Specific aim 1

The analysis for Aim 1 will compare the randomized NIATx-IF versus NIATx-EF on our primary implementation outcome of the proportion of MOUD patients receiving medication within 72 h of OUD diagnosis over time. For the changes over time in the proportion of patients initiating MOUD within 72 h of diagnosis, we expect 48 new patients with OUD each quarter for each of the 54 expected sites that are randomized to either IF or EF. We will use 2-level latent growth models of 10 quarters of outcome data with individual-level binary outcomes of MOUD within 72 h. Specifically, we assume that the number of patients who start MOUD at the *i*th site and *t*th time point, *i* = 1,…,54 and *t* = 1,…,10, are all independent binomials with success probability pit on 48 individual patient trials. Here logit (pit) = ai + bi t + εit with random intercepts ai and random slopes bi = β0 + β1 Fi + εi and Fi is the indicator of facilitator condition and the effect is tested through coefficient β1.

To account for multiple comparisons in secondary analyses, we will use a false discovery rate to reflect how many subscales are assessed for each measure. In addition, we will use exploratory graphical measures, such as empirical *q*-*q* plots, to compare all the subscales’ differences by intervention condition [81]. For the analyses of the stagewise implementation to target outcomes, we will assess the degree to which all the sites eventually achieve the criterion. This criterion is defined as an IMAT Total Score ≥ 3, the presence of an integrated prescriber for MAT, and at least 50% of patients with OUD on MOUD. This is accounted for by computing the proportion of the study sites that achieve criterion in their respective phase and computing two different proportions, one for each facilitation condition, much the same way that SMART designs are evaluated for overall optimal impact.

#### Specific aim 2

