### Power calculations

For power analyses, we used Monte Carlo methods. Starting at randomization with both conditions at 20%, we have 80% power to detect a change where 54% of the patients in sites in the better facilitation condition are provided MOUD by the last quarter, compared to 45% of the patients in the poorer performing arm. This power calculation allows for moderate variation among the sites’ rates at baseline, in the slopes, and at each measurement time. The approach to the effectiveness measure, 6-month retention rate, will proceed similarly.

We will utilize latent linear growth modeling to understand the impact on the secondary composite continuous measure outcomes (e.g., IMAT; SIC). The impact will be identified as the difference in slopes for the two implementation strategy conditions, fit using maximum marginal likelihood, and tested using a Wald-type test on the difference in slopes divided by the corresponding standard error. Monte Carlo simulation was used to examine how the model’s parameters affect statistical power. With type I error of 5%, and conservative measurement error of 20% at each time point, we have 80% power to detect an effect size of 0.77 (54 randomized sites) and conservatively 0.81 (49 randomized sites). We note that in a previous head-to-head randomized implementation trial of 51 sites, we were able to find significant differences in implementation outcomes.

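### The primary 72-hour access outcome has two conflicting denominators (patients prescribed MOUD, or all new patients with OUD), so the stated 80% power does not carry over to the Table 3 definition

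*Protocol article*

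**What the plan says.** The denominator of the 72-hour outcome appears in three places in the protocol article.

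- **Table 3 (Implementation outcomes, Aim 1).** Access is "The proportion of patients prescribed MOUD who start the medication within 72 h of OUD diagnosis". A further clause starts the 72-hour clock differently for patients who need detoxification before naltrexone.
- **Data analysis, Specific aim 1.** The opening sentence names "our primary implementation outcome of the proportion of MOUD patients receiving medication within 72 h of OUD diagnosis over time", which agrees with Table 3. The next sentence moves to "we expect 48 new patients with OUD each quarter for each of the 54 expected sites that are randomized to either IF or EF". The model then takes the site-by-quarter counts, which "are all independent binomials with success probability pit on 48 individual patient trials". The counts are described as "the number of patients who start MOUD at the" given site and time point, and that clause does not repeat the 72-hour limit.
- **Power calculations.** Both arms start at 20%. The 80% power is to detect a difference in which "54% of the patients in sites in the better facilitation condition are provided MOUD by the last quarter", against 45% in the other arm. The 72-hour limit is not repeated, and there is no restriction to prescribed patients.

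**The concern.** The 48 trials can be the denominator only if the outcome is counted among all new patients with OUD. If it is counted among prescribed patients, the number of trials is the number prescribed, which the article never states. The Background puts current MOUD receipt in specialty addiction treatment at 15% of patients with OUD, so the two denominators could differ several-fold.

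Three things are at stake.

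1. **Power.** The figure was derived for one outcome and would be quoted for another.
2. **Comparability of the arms.** Being prescribed MOUD happens after randomization and is something facilitation is meant to increase. Among prescribed patients only, the arms may contain differently selected patients.
3. **Undefined values.** A site and quarter with no prescriptions gives 0/0 under Table 3 but 0/48 under the model.

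With both definitions in the text, the analyst could choose between denominators that need not favour the same arm.

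**Working it through.** **Inputs from the article:** 54 randomized sites; 48 new patients with OUD per site and quarter; 10 quarters; 20% at randomization; 54% versus 45% at the last quarter; 80% power; a model with random intercepts, random slopes and a site-by-quarter error, in which facilitation enters through the slope. **Assumed:** 27 sites per arm, two-sided 5% (the article states 5% only for the continuous outcomes), and all variance components, which it describes only as moderate.

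**Step 1: the planned effect.** Logits are logit(0.20) = -1.386, logit(0.54) = 0.160 and logit(0.45) = -0.201. Over t = 0 to 9 the slopes are (0.160 + 1.386)/9 = 0.1718 and (-0.201 + 1.386)/9 = 0.1317. The difference is 0.0401 per quarter.

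**Step 2: can 80% be reproduced at 48 trials?** For one site, the binomial variance of the slope is 1/Σ w(t - t̄)², with w = 48·p(1 - p) and t̄ the w-weighted mean of t. This gives 0.00122 in the better arm and 0.00125 in the poorer arm. The variance of the slope difference is (0.00122 + 0.00125 + 2e)/27, where e is the extra between-site variance of a slope.

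- With e = 0, the standard error is 0.00956, z = 4.20 and power is 98.7% (98.1% by simulation).
- Power is 80% when e = 0.00153, equivalent to a slope SD of about 0.039 alone or a site-by-quarter SD of about 0.36 alone. The standard error is then 0.0143 and z = 2.80.

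So 80% is attainable with 48 trials and is not shown to be wrong. It cannot be reproduced exactly without the variance components.

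**Step 3: the Table 3 denominator (illustration).** Keep e = 0.00153 and the same rates, and replace 48 by the number prescribed. That number is not in the article.

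| Assumed share of the 48 prescribed | Trials per site and quarter | Power |
|---|---|---|
| 100% | 48 | 80% |
| 75% | 36 | 74% |
| 50% | 24 | 64% |
| 20%, constant | 9.6 | 39% |
| rising from 20% to 54% / 45% | 9.6 to 25.9 / 21.6 | 51% |

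In the last row the binomial slope variances are 0.00369 and 0.00415, the standard error is 0.0201 and z = 1.99.

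**Step 4: sensitivity to the modelling choice.** Steps 2 and 3 estimate each site's own slope. A generalized least squares version with a common intercept in the two arms, closer to the written model, uses t = 1 to 10 with 20% at t = 0, so the slope difference is 0.361/10 = 0.0361. With intercept SD 0.3 to 0.8 and site-by-quarter SD 0.1 to 0.3, the slope SD that gives 80% at 48 trials is 0.014 to 0.036. With the rising denominator, power is then 55% to 71%. Taken with the 51% above, the range is roughly 50-70%.

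**Step 5: can the ranking reverse?** Invented figures per 48 patients with OUD: arm 1 prescribes to 15 and starts 12 in time; arm 2 prescribes to 30 and starts 21 in time. Among those prescribed, 12/15 = 80% against 21/30 = 70% favours arm 1. Among all with OUD, 12/48 = 25% against 21/48 = 44% favours arm 2. This shows that a reversal is possible, not that it is expected.

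**The case against.** The strongest reply is that this is loose wording around one outcome. Specific aim 1 describes patients initiating MOUD within 72 h and individual binary outcomes of MOUD within 72 h, so the modelled outcome is a 72-hour one, and the phrase about being provided MOUD in Power calculations is probably shorthand for it. That stands: a reader might count three different endpoints, but the text supports only two conflicting denominators plus an omitted time limit.

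A reader might also infer that the Table 3 measure is biased. The documents do not show this. Timeliness among prescribed patients is a recognisable step in the care cascade and a legitimate descriptive quantity. The risk arises when it is used to compare randomized arms, and no prescribing rate by arm is given from which a size or direction could be computed.

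Nor do the documents show that sites without a prescriber will drop out of the analysis. The statement "Specifically of all addiction treatment programs in the state, 72% do not offer MOUD" describes programs statewide, not randomized sites. Randomization comes at 12 months, after feedback and, where needed, the workshop. A program can be randomized for missing any one of three targets, and the Discussion recognises linked or coordinated access. How many randomized sites will have no prescriptions is unknown.

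Finally, the power figures above apply the 20%, 45% and 54% rates to a denominator for which they were not stated. That is correct, and it is why they are illustrations. None of these replies says which denominator the primary analysis uses.

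**Conclusion.** The point holds as an internal contradiction about the primary outcome. Table 3 and the opening sentence of Specific aim 1 count among patients prescribed MOUD; the model and its 48 trials count among new patients with OUD. The stated 80% power is attainable for the second but does not carry over to the first, for which power is unknown.

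The roughly 50-70% rests on assumed variances calibrated to 80% at 48 trials, unchanged planning rates, and a prescribing share that rises with those rates. The selection problem is a risk that could reverse the ranking of the arms, with size and direction unknown. The outcome is undefined in any site and quarter with no prescriptions, with unknown frequency. Because this is the only randomized comparison, the definition should be settled before analysis.

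**What to change.** Use one definition in Table 3, Specific aim 1 and Power calculations. The one that matches the written model is patients starting MOUD within 72 h divided by all new patients with OUD at the site in that quarter, with Table 3's existing naltrexone timing clause kept. A site and quarter with no prescriptions then counts as zero, not as undefined.

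- Align Table 3 and the opening sentence of Specific aim 1 with that denominator.
- Add the 72-hour limit to the sentence defining the binomial counts and to the power sentence.
- Confirm or restate the 20%, 45% and 54% rates and the 80% power for that outcome, and give the variance components used.
- Report the proportion among prescribed patients as a secondary descriptive measure.

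If the planning rates already refer to that outcome, the cost is wording only; if not, the power simulation must be rerun. The small downside is that patients who decline or do not need MOUD count as not accessed. If the sponsor prefers the prescribed-patient outcome as primary, the number of trials, the planning rates and the power must be rederived for it, and the handling of site-quarters with no prescriptions stated.
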